### Outcomes

The primary effectiveness outcome for the main trial will be a continuous composite score that averages standardized improvements for each of the four targeted behavioral outcomes: two diet outcomes (increasing fruits and vegetables servings to ≥ 4.5 daily and decreasing saturated fat) and two activity outcomes (increasing physical activity to 150 min per week and reducing daily time spent on targeted recreational screen pastimes to 90 min per day) from baseline, week 13 (month 3) and week 39 (month 9). These outcome data will be obtained from the app data rather than from a separate food or activity frequency questionnaire. This primary outcome will be standardized on a common scale corresponding to an effect size by creating a Z- score. Secondary (exploratory) outcomes include change in biomarkers, including blood pressure, lipids, A1C, waist circumference, and BMI.

### Analyses

The trial was powered to have approximately 80% power to detect an intervention effect of 0.4 for the primary outcome when the sample size is 240 (120 per group), with a two-sided significance level of 0.05. To ensure adequate power after accounting for attrition and missing data, the primary analysis will include all 350 individuals randomized to treatment. We anticipate that (1) secondary comparisons will adjust for potential confounders, and (2) analyses for effects over time will be made using repeated measures. Including confounders reduces variability and can help to increase power. Further, because repeated measures are correlated, using the multiple measures in models also helps to increase power. For example, when the sample size is 120 participants per group (*N* = 240), a repeated measures analysis will have at least 80% power to detect the group*time interaction assuming that the groups start at baseline with no difference and then have effect sizes at weeks 13 (month 3) and 39 (month 9) of approximately 0.4 and 0.45, respectively.

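### The stated power of about 80% for an effect of 0.4 with 240 participants does not follow from its own inputs, which give about 87%; the error is conservative and needs a wording correction.

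*Protocol article*

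**What the plan says.** The Analyses section of the protocol article gives the sample-size basis for the primary outcome: "approximately 80% power to detect an intervention effect of 0.4 for the primary outcome when the sample size is 240 (120 per group"). The test level is given as 5%, two-sided. The Outcomes section gives the scale. The primary outcome is a continuous composite that averages standardised improvements in four behaviours, and "This primary outcome will be standardized on a common scale corresponding to an effect size by creating a Z- score".

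Attrition has its own sentence in Analyses: "To ensure adequate power after accounting for attrition and missing data, the primary analysis will include all 350 individuals randomized to treatment". No attrition rate is given.

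The same paragraph makes a second power claim at 120 per group: "a repeated measures analysis will have at least 80% power to detect the group*time interaction". It assumes no difference at baseline and effects of about 0.4 at week 13 and 0.45 at week 39. No correlation between visits is given.

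**The concern.** The first statement prints the effect, the number per group, the significance level, its sidedness and the power together. Any four of these determine the fifth for a simple two-group comparison, and here they do not agree.

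The allowance for missing data does not explain the gap. The text deals with attrition separately through the 350, so 240 reads as the number with outcome data.

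What is at stake is whether the reader can trust the stated basis for the trial's size. Several unprinted inputs would bring the power back to 80%, and they describe different trials. One of them, a smaller significance level, would conflict with the 0.05 in the text. The attrition sentence adds a smaller problem: it presents the choice of analysis population as the means of keeping power. Randomising more people does that; including people whose outcomes are missing does not.

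**Working it through.** **Inputs.** Effect δ = 0.4, n = 120 per group, two-sided α = 0.05 (all Analyses). SD = 1, from the Z-score scale (Outcomes). The test is not named, so an unadjusted two-sample comparison of means is assumed.

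**1. Power at the stated size.**
Normal approximation: power = Φ(δ√(n/2) − 1.960).
0.4 × √60 = 3.098; 3.098 − 1.960 = 1.138; Φ(1.138) = 87.3%.
The exact noncentral t gives 87.0%. The stated figure is about 80%, so it is not reproduced. The type II error is 13%, not 20%.

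**2. Size needed for 80%.**
n per group = 2(1.960 + 0.842)²/δ² = 2 × 7.85/0.16 = 98.1, so 99.
The noncentral t gives 99.08, so 100 per group (80.4% power). The total is 198 to 200, against 240 stated.

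**3. Effect detectable with 80% power at 120 per group.**
δ = (1.960 + 0.842) × √(2/120) = 2.802 × 0.1291 = 0.362; the noncentral t gives 0.363.

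**4. Inputs that would recover about 80% at 240 (noncentral t).** None is stated for this calculation.

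| Added assumption | Power for 0.4 |
|---|---|
| Two-sided α = 0.025 (for example, split over weeks 13 and 39) | 80.0% |
| Design effect 1.2 (240/1.2 = 200) | 80.4% |
| 15% loss taken out of 240 (204 left) | 81.1% |
| 0.4 in raw SD units, analysed as change with correlation 0.4 (0.4/√(2 × 0.6) = 0.365) | 80.4% |
| One-sided α = 0.05 (normal approximation) | 92.7%, further away |

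**5. The repeated-measures statement.** Take group differences of 0, 0.4 and 0.45 at the three times, SD 1 and equal correlation r between visits. The 2-df interaction then has noncentrality
λ = (120/2) × [2(0.4²) + 2(0.45²) − 2(0.4)(0.45)] / [3(1 − r)] = 60 × 0.365/[3(1 − r)] = 7.3/(1 − r).

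| r | λ | Power |
|---|---|---|
| 0.2 | 9.1 | 77% |
| 0.3 | 10.4 | 83% |
| 0.5 | 14.6 | 94% |

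The claim of at least 80% is therefore reasonable at moderate correlation.

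**6. The 350.** 1 − 240/350 = 31.4%, the loss that would leave 240 with outcomes. With no loss (175 per group), power for 0.4 is 96.2% and the effect detectable with 80% power is 0.300.

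**The case against.** The strongest reply is that the article never says its 80% comes from an unadjusted two-sample test. The outcome is an improvement from baseline, so a change-score calculation is plausible, and the fourth row of the table in step 4 shows that an ordinary correlation would give 80%. A journal article commonly leaves the test, the correlation and the variance to the full protocol or analysis plan. The error also runs in the safe direction.

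Part of this stands. The mismatch may come from an omitted input and not from a slip, and the consequence for the design is nil. But the article prints a complete set of inputs that do not agree, and the word 'approximately' does not cover 7 points. The input that fits 120 per group most closely, α = 0.025, contradicts the printed 0.05. A change-score basis in raw SD units sits poorly with an outcome already put on an effect-size scale.

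A reader might also draw four stronger conclusions, which the document does not support:

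- *The scale of 0.4 is undefined, because an average of four Z-scores need not have SD 1.* The Outcomes section applies the Z-score to the primary outcome itself, which is the composite. That supports SD = 1, and the 87% depends on it.
- *This is the trial's only justification of size.* The repeated-measures statement is a second one at the same 240, and it is plausible.
- *The sponsor planned for 31% loss.* No rate is stated. The figure is derived from 350 and 240, and 240 may be only a floor.
- *An allowance for clustering is built in.* Nothing in the Analyses section says so. A design effect of 1.2 is only what would close the gap.

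**Conclusion.** The point holds as an error in a stated figure. With SD = 1 and a plain two-group comparison at two-sided 0.05, 240 participants give about 87% power for an effect of 0.4, not about 80%. Equivalently, 80% needs about 200 participants, or applies to an effect of about 0.36.

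The trial is not underpowered by this error, and neither 240 nor 350 has to change. The repeated-measures claim is not in dispute. The conclusion rests on two assumptions: that 0.4 is in SD units of the analysed composite, which the Outcomes section supports, and that no further input was used, which the document neither states nor rules out.

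The attrition sentence is a lesser matter of wording. Its likely meaning is that 350 are randomised so that enough remain after losses, and that all are analysed. As written, it credits the analysis population with protecting power.

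**What to change.** Choose one of two corrections in the Analyses section:

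- If no further input was used, restate: *240 analysed (120 per group) gives about 87% power for 0.40, or 80% power for 0.36, in SD units of the composite, at a two-sided level of 0.05.*
- If the 80% rests on a further input (a split of alpha over week 13 and week 39, a design effect, a change-score correlation, or loss taken out of the 240), state that input with its value. If it is an alpha split, reconcile it with the printed 0.05.

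In either case, reword the attrition sentence: *350 are randomised to allow for attrition while leaving at least 240 with outcome data; all randomised participants are included in the primary analysis.* If a loss figure is given, describe up to 31% as what 350 and 240 imply, unless the sponsor confirms a planning rate.

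The cost is two or three sentences. Enrolment, assessments and the analysis stay as they are, unless an alpha split was in fact intended; the stated significance level would then need correcting too.

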## Discussion

Adapting, implementing, and evaluating existing evidence-based interventions for underserved populations has the potential to improve health equity with greater efficiency, effectiveness, and cost savings than initiating a program from scratch. However, few implementation studies employ a community-engaged process that incorporates cultural and contextual adaptation, thereby forfeiting the opportunity to develop appropriate, scientifically rigorous, sustainable interventions to achieve health equity [21]. Lack of cultural and contextual adaptation leads to inappropriate implementation, sacrificing the utility of programs where they are most needed [13, 21, 41].

In this article, we aimed to address the notable lack of explicit description on steps to adapt evidence-based interventions. Most advances in promoting the uptake and implementation of effective interventions have occurred in clinical or health systems settings [42, 43] and few provide extensive details on how this adaptation actually takes place. Given the iterative nature of adaptation, aligning with the context and culture of underserved populations requires an extensive and prolonged community engagement in the developmental phase of adaptation [22, 44].

We also have updated the literature to incorporate recent trends in technology use among rural residents, throwing off old assumptions of inadequate use, preference, or facility with such approaches. Ironically, increasing smart phone use, internet access, and broadband internet connectivity in rural areas contributes to sedentary behavior while also making the mHealth interventions that reach rural residents possible.

Our adaptation approach reveals the steps we took to ensure a balance between fit with the local population and adherence to standards of fidelity with the existing evidence-based intervention. While our iterative formative research and pilot testing has set the stage for culturally appropriate adaptation of this evidence-based intervention, it remains undetermined whether programs such as MBC2, developed and implemented in an urban environment, can remain efficacious when implemented in rural communities [45, 46]. Our next step is to implement and evaluate whether we have positively impacted participants’ health through this community-engaged, culturally, and contextually appropriate protocol.

## Data Availability

The datasets used and/or analyzed during the current study are available from the corresponding author on reasonable request. Information regarding data collection methods, descriptions of study instruments, and data collection forms is also available upon request.

## Abbreviations

Hemoglobin A1C level (A1C): A measurement of blood sugar levels, commonly used to diagnose and treat prediabetes and diabetes.
BMI: Body-mass index
CAB: Community Advisory Board
CFIR: Consolidated Framework for Implementation Research
COBRE: Center for Biomedical Research Excellence
FG: Focus groups
KII: Key informant interviews
KY: Kentucky
MBC2: Make Better Choices 2
mHealth: Mobile health
MVPA: Moderate vigorous physical activity
NIH: National Institutes of Health
REDCap: Research Electronic Data Capture
RUCA: Rural–urban commuting area
SUDS: Subjective Units of Distress Scale
